### Data analysis plan

All statistical analyses will be performed based on an intent-to-treat principle. We will first describe the characteristics of participants in each group, using means and standard deviations (continuous variables) or percentages (categorical variables). The groups will be compared at baseline (T0) using Student’s T test or the Chi-square test. Wherever possible, comparisons will be made between patients who agreed to participate in either phase of the study and those who refused, in order to document biases related to refusals. For outcome indicators at 3 months (self-efficacy, self-management practices, health habits, activation and psychological distress), groups will be compared at T1 using analysis of covariance adjusted for T0 scores. For indicators measured at six months (empowerment, quality of life and use of care), repeated measures analysis of variance will compare change over time in the two groups. In all cases, if the groups initially differ with regard to certain characteristics despite randomization, analysis will be adjusted to take into account the relevant variables. In addition, if a nurse effect is present (non-null intracluster correlation), despite efforts at standardization, multi-level analysis will be conducted to take this into account.

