#### Case management by FMG nurses

The first component of the intervention is the follow-up offered under the case management process, which is seen as a collaborative, dynamic and systematic approach to ensure and coordinate care and services for a defined clientele based on interdisciplinary practice. Here the nurse evaluates, plans, implements, coordinates and prioritizes options and services according to patient health needs, in close collaboration with the involved partners [40]. The intervention focuses on four main components: (1) A thorough evaluation of patient needs and resources; (2) Establishment and maintenance of a patient-centred, individualized service plan (ISP); (3) Coordination of services among partners; and (4) Self-management support for patients and families [41].

The main duties and responsibilities of nurses in case management will be to: (1) Evaluate the patient’s situation and needs and involve the family, with the patient’s consent; (2) Identify which partners of the CSSS and of the community network to involve; (3) Jointly plan patient follow-up by establishing an ISP with the partners and with the active participation of the patients and family — minimum of two ISP per patient: one to initiate the intervention and the other approximately 3 months later; (4) Negotiate the services and defend the rights and interests of the individual; (5) Coordinate care and services; (6) Monitor the ISP application; (7) Educate and support the person. The ISP formulation stage will be oriented towards a self-management support approach that will emphasize the following: the patient’s potential; setting objectives according to his or her perspective; developing problem-solving skills; and using the patient’s usual support system [42]. Home visits by the nurse may be required, when justified — as in the case of reduced mobility or if a home assessment is needed — while avoiding overlap with home support services already offered.

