### Measures

The variables defined within the logic model will be measured using instruments that are well known and have been validated in studies similar to the one proposed.

The proximal outcomes, evaluated at T0 (recruitment period), T1 (3 months) and T2 (6 months) for both groups (see Table 2), will be: (1) self-efficacy measured with the *Self-Efficacy for Managing Chronic Disease* scale [61]; (2) self-management practices, with the *Self-monitoring and Insight* sub-scale of the *health education impact questionnaire* (heiQ [62,63]; (3) health habits, using the questionnaire developed as part of the PRECISE study [64]; (4) patient activation, with the *Patient Activation Measure*[65]; and (5) psychological distress, with the *Psychological Distress Scale*[66].

**Table 2 T2:** Proposed study plan

	**Visit 1**	**Visit 2**^**1**^	**Visit 3**	**Visit 4**	**T3**^**2**^
	**T0**		**T1**	**T2**	
Time from the start of the intervention	−2 weeks	0	3 months	6 months	12 months
Verification of eligibility	√				
Informed consent	√				
Covariables: Socioeconomic level, social isolation, literacy, mental health and multimorbidity	√				
Proximal outcomes: Personal self-efficacy, self-management practices, lifestyles, activation and psychological distress	√		√	√	
Intermediate outcomes: Empowerment, quality of life and use of services	√			√	√

^1^ Visit 2 will mark the beginning of the intervention. This will be two weeks after randomization for the experimental group and 6 months after randomization for the control group.

^2^ For the experimental group and use of services only.

Intermediate outcomes, evaluated at T0 and T2 (see Table 2), will include: (1) empowerment, measured with the heiQ scale [62]; (2) quality of life, measured with the SF-12v2 scale [67]; and (3) the use of health services, measured using clinical data from the CSSS (with Magic Chronique software by MediaMed) for hospitalizations, emergency room visits and CSSS services (e.g., psychosocial services or specialized services related to the specific CD), and electronic data on visits with physicians and nurses in the FMG.

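### At six months empowerment and quality of life are compared by change, which is valid but no more precise than the T0-adjusted ANCOVA used at 3 months, and the T2 proximal scores have no stated analysis

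*Protocol article*

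**What the plan says.** The Data analysis plan of the protocol article sorts outcomes by time point and gives each set a method.

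- Proximal outcomes: "For outcome indicators at 3 months (self-efficacy, self-management practices, health habits, activation and psychological distress") come first, and for these "groups will be compared at T1 using analysis of covariance adjusted for T0 scores".
- Intermediate outcomes: "For indicators measured at six months (empowerment, quality of life and use of care") follow, and for these "repeated measures analysis of variance will compare change over time in the two groups".

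The same paragraph adds two conditional steps: adjustment if the arms differ at baseline on some characteristics, and multi-level analysis if a nurse effect is found.

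The Measures section gives the schedule. Proximal outcomes are "evaluated at T0 (recruitment period), T1 (3 months) and T2 (6 months) for both groups". For the others it says "Intermediate outcomes, evaluated at T0 and T2 (see Table 2"). The second footnote to Table 2 limits the 12-month visit (T3) to service use in the experimental group. Empowerment and quality of life therefore have two measurements in each arm.

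**The concern.** There are two separate matters.

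First, one paragraph uses the T0 score as a covariate at 3 months and subtracts it at six months, without giving a reason. With only two time points, subtracting the baseline uses it less efficiently than regressing on it. What is at stake is precision on empowerment and quality of life, which also feed the cost-effectiveness ratios in the economic analysis.

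Second, the proximal outcomes are collected at the end of the six-month intervention, but the only comparison written down is at its midpoint. That is about when the second service plan is due under Case management by FMG nurses ("one to initiate the intervention and the other approximately 3 months later"). A proximal effect that grows or fades between 3 and 6 months would not appear in the stated comparison. With five outcomes and an open time point, the choice between 3 and 6 months could also be made after the data are seen.

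**Working it through.** **Inputs from Sample size and statistical power:** 200 per group, 25 patients per nurse, intracluster correlation (ICC) at most 0.10, standardized effect 0.5, two-sided α 0.05, power 80%. **Assumed:** r = 0.3, 0.5 and 0.7, because the article gives no T0–T2 correlation, and equal variances at T0 and T2.

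**The plan's own figure.** Without clustering, 63 per group are needed. The design effect is 1 + 24 × 0.10 = 3.4, and 63 × 3.4 = 214. With 200 per group the power is 77% and the detectable effect is 0.517, which rounds to the stated 0.5. The calculation uses no gain from baseline adjustment. Nothing below depends on the small gap from 80%.

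**Equivalence.** With two time points, the group-by-time F statistic of a repeated-measures ANOVA is the square of the t statistic comparing mean change between groups.

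**Without nurse clustering** (variances in units of SD²):

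- Change: 2(1 − r). ANCOVA: 1 − r². Ratio of ANCOVA to change: (1 + r)/2.
- r = 0.3: 0.91 against 1.40, ratio 0.65, a 35% cut.
- r = 0.5: 0.75 against 1.00, ratio 0.75, a 25% cut.
- r = 0.7: 0.51 against 0.60, ratio 0.85, a 15% cut.

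A simulation with 200 per arm gave change-to-ANCOVA variance ratios of 1.51, 1.32 and 1.21 (theory 1.54, 1.33 and 1.18). Both estimators were unbiased: for a true effect of 0.30, the means lay between 0.297 and 0.300. Below r = 0.5 the change score has a larger variance than the T2 score alone (1.40 against 1 at r = 0.3).

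**With nurse clustering at ICC 0.10.** Assume that nurse effects arise after T0, through delivery of the intervention, so that neither method removes them. Split the T2 variance into 0.10 between nurses and 0.90 within. In units of 1/200 per arm, the nurse part is 25 × 0.10 = 2.5. The arm totals are:

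- Change: 2.5 + 0.9 × 2(1 − r). ANCOVA: 2.5 + 0.9 × (1 − r²).
- r = 0.3: 3.760 against 3.319, a 12% cut.
- r = 0.5: 3.400 against 3.175, a 7% cut.
- r = 0.7: 3.040 against 2.959, a 3% cut.

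Power at effect 0.5 uses SE = √(2 × total/200). For change it is 73%, 77% and 82%; for ANCOVA it is 78%, 80% and 83%.

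If only the intervention arm is clustered, the control arm contributes the 0.9 term alone:

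- r = 0.3: 5.020 against 4.138, an 18% cut.
- r = 0.5: 4.300 against 3.850, a 10% cut.
- r = 0.7: 3.580 against 3.418, a 5% cut.

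Power is then 88%, 93% and 96% for change, and 94%, 95% and 97% for ANCOVA.

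**Proximal outcomes.** No arithmetic applies. Measures and Table 2 schedule T0, T1 and T2 in both arms. The Data analysis plan names all five outcomes in its 3-month list and none in its six-month list. One of the two post-baseline waves has no stated comparison.

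**The case against.** The case against the first part is that repeated-measures ANOVA is a legitimate analysis of a randomized comparison, and that different methods for different outcome sets are not a contradiction. That stands. A reader might infer that the change analysis is biased. The simulation shows no bias, and the loss is one of precision only.

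A reader might also carry the 35%, 25% and 15% straight into this trial, or multiply them through the whole design effect, which would give 63% power for change against 81% for ANCOVA at r = 0.3. That treats nurse variance as if the T0 score predicted it. The article ties nurse effects to the case management nurses' work, which begins after T0, so the document gives no support for that reading. At the planned ICC the power difference is about 1 to 5 points. At ICC 0 the percentages hold, but power at effect 0.5 is at least 98.8% by either method.

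The conditional steps in the plan do not remove the point. Adjustment is triggered by observed baseline differences, and multi-level analysis by a nurse effect. Neither says that the T0 score becomes a covariate.

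On the second part, the objection is that a journal article condenses a fuller plan, and that testing proximal outcomes early fits the split between proximal and intermediate effects. Both are fair. A reader might infer that the T2 proximal data will go unanalysed, or that six months must be the main contrast. The article says neither: an analysis plan not shown may cover T2, and objective 2 fixes no time point. What remains is that the article allocates each outcome to a time point and leaves out one that it schedules.

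**Conclusion.** The point holds as a matter of efficiency and completeness. It is not an error of validity.

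For empowerment and quality of life, the planned test is a change-score comparison that ANCOVA on T0 equals or betters in precision. The gain is 15% to 35% of the variance without nurse clustering. It is about 3% to 12% at the plan's maximum ICC with both arms clustered, and 5% to 18% if only the intervention arm is. These figures rest on r between 0.3 and 0.7, equal variances at T0 and T2, and nurse effects arising after T0. The gain is modest at the planned ICC but costs nothing, because the baseline is already collected.

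For the proximal outcomes, the schedule and the analysis section do not match: T2 is collected in both arms and no comparison at T2 is stated. The investigators should settle this before the data are seen.

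Use of care shares the six-month sentence, but the ANCOVA recommendation here is confined to the two questionnaire scales.

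**What to change.** Replace the six-month method for empowerment (heiQ) and quality of life (SF-12) with ANCOVA of the T2 score adjusted for the T0 score, with a nurse random effect where clustering is present.

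For the five proximal outcomes, fit one mixed model to T1 and T2 with T0 as covariate, group, visit, group-by-visit and a nurse effect, allowing for correlation between a patient's two visits. Report both the 3-month and the 6-month contrasts, and have the investigators state in advance which one leads. The model also keeps patients who miss one of the two follow-ups, which sits well with the intent-to-treat principle, although that principle does not require this particular model.

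The cost is a few sentences of analysis wording. No visit, instrument or patient is added. If a separate analysis plan already covers T2, a cross-reference settles the second part.

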## Background

Because of their high prevalence and significant effects, chronic diseases (CD) pose a major challenge for health care and social services, for society and for the persons affected [1]. These individuals often have to make important day-to-day adjustments as a result of disability, loss of income, and a declining quality of life [2,3]. It is now recognized that primary care should be central to the customized and effective management of CD [4,5], and that innovative strategies targeting the current organization of primary care must be offered and evaluated to better support the individuals affected [1], particularly the most vulnerable [6]. To meet the complex needs of people with CD and to reduce societal consequences, primary care must provide a range of services that are interdisciplinary, person-centred and adjusted to the individual’s current health conditions and characteristics [7,8]. These services must also be oriented towards self-management, where the people affected and their families are called upon to play a greater role in the management of their health [1,7,9].

A number people with CD require higher intensity care because of personal characteristics that increase their vulnerability. This applies especially to the socioeconomically disadvantaged [10,11] and to those who present a comorbid mental health condition [12,13] or multimorbidity (two or more CD) [13,14]. In addition to a compromised quality of life and an increased risk of social isolation, these individuals have problems complying with treatment, adopting healthy behaviours and managing their health. This can result in increased services use, like emergency department visits and hospitalizations [15,16]. Case management strategies could be developed to address the vulnerability factors of frequent users in order to prevent inequities in health care and related costs [17].

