A number of covariables will also be documented (T0) to describe participant characteristics: (1) socioeconomic status with family income and patient perceptions of his or her economic situation; (2) social isolation, measured with the social isolation subscale of the *Nottingham Health Profile*[68]; (3) literacy, measured with the *Newest Vital Sign*[69]; (4) mental health, measured with the *Hospital Anxiety and Depression Scale* (HADS) [70,71]; and (5) multimorbidity, measured with the *Disease Burden Morbidity Assessment* (DBMA) [72]. French versions are available for all validated instruments. When selecting data collection instruments, valid shorter versions were preferred to reduce completion time. Considering the circumstances of the vulnerable clientele, questionnaires will be self-administered in the presence of a research assistant who will provide the required assistance to the participant, ranging from minimal supervision to reading all the questions, if and when needed. If the patient cannot travel, the questionnaires can be administered by telephone or at the participant’s home.

The evaluation component will be conducted according to the study plan described in Table 2.

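### Beyond each outcome's own T0 value, the baseline covariables enter the model only if the randomized groups are seen to differ at T0, so chance imbalance rather than prognostic value selects the adjustment

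*Protocol article*

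**What the plan says.** Three parts of the protocol article bear on this.

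- **Data analysis plan, fixed part.** For the 3-month outcomes, "groups will be compared at T1 using analysis of covariance adjusted for T0 scores". For the six-month outcomes, "repeated measures analysis of variance will compare change over time in the two groups". The outcome's own baseline is therefore always used, as a covariate at 3 months and as a time point at six months. No other covariate is named for either model.
- **Data analysis plan, conditional part.** "The groups will be compared at baseline (T0) using Student’s T test or the Chi-square test". Later in the same paragraph, and for every outcome: "if the groups initially differ with regard to certain characteristics despite randomization, analysis will be adjusted to take into account the relevant variables". The article does not say how large a difference counts or which variables are relevant.
- **Measures.** "A number of covariables will also be documented (T0) to describe participant characteristics". Five domains follow: socioeconomic status (family income and perceived economic situation), social isolation, literacy (Newest Vital Sign), mental health (HADS) and multimorbidity (DBMA).

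The Background treats three of these as markers of vulnerability: socioeconomic disadvantage and "those who present a comorbid mental health condition [12,13] or multimorbidity (two or more CD"). Of the difficulties such patients have with treatment and self-care, it says: "This can result in increased services use, like emergency department visits and hospitalizations". Service use is a trial outcome. The Study population section specifies simple randomization.

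**The concern.** Adjustment is useful when a covariate predicts the outcome, and a comparison of randomized groups at baseline does not measure that. Under simple randomization any T0 difference is due to chance. A weak predictor can differ by chance and enter the model, while a strong one that happens to be balanced stays out and its precision is lost.

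Two things are at stake. First, the model behind each reported estimate is settled only once the baseline data are in, so the estimate cannot be fully described in advance. Second, covariables that are collected from every participant anyway would usually do nothing for precision, although the article's own rationale treats several of them as prognostic.

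**Working it through.** The plan gives no figure for this rule, and its sample-size section uses no covariates, so there is nothing of its own to reproduce. The check has three steps.

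**1. How often chance alone would switch the model.**

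Inputs: five domains under Measures. Counting the two socioeconomic measures separately gives 6. Also scoring HADS as separate anxiety and depression parts (an assumption) gives 7. The 5% level for each baseline test is assumed, because the article gives no threshold. Independence of the tests is assumed.

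Formula: P(at least one difference) = 1 − 0.95^k.

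- k = 5: 1 − 0.95^5 = 0.226
- k = 6: 1 − 0.95^6 = 0.265
- k = 7: 1 − 0.95^7 = 0.302

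The range is about 23% to 30%. Positive correlation among the covariables would lower it.

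**2. What a fixed list could gain.**

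The article gives no R-squared, so a range is assumed. If the covariables jointly explain a share R² of the variance left after T0 adjustment, residual variance is multiplied by (1 − R²) and the standard error by √(1 − R²).

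- R² = 0.10: √0.90 = 0.949, so the standard error is about 5% smaller
- R² = 0.20: √0.80 = 0.894, so the standard error is about 11% smaller

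**3. What the stated rule delivers instead.**

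This was simulated with 200 per arm, five independent covariates, 6,000 replicates per setting and no nurse clustering. The outcome has unit variance and stands for what remains after T0 adjustment. The rule was taken as adjusting for any covariate with baseline p < 0.05. The true difference of 0.28 SD was chosen so that the analysis without covariates has about 80% power. It is not the trial's target.

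| Assumed R² | Power, no covariates | Power, fixed list | Power, stated rule | Rejection under the null, stated rule |
|---|---|---|---|---|
| 0.10 | 80% | 83% | 80% | 4.9% |
| 0.20 | 79% | 87% | 80% | 4.3% |
| 0.30 | 80% | 91% | 81% | 3.9% |

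The rule led to adjustment in 22% to 23% of simulated trials, in line with step 1 for k = 5. Its estimate differed from the fixed-list estimate with an SD of 0.03 to 0.05 outcome SD, against a standard error of about 0.10. So the rule performs much like using no covariates, and under the null it rejects no more often than the nominal 5%.

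**The case against.** The strongest defence has four parts.

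- **The most important covariate is already in.** This stands. The outcome's own T0 value is normally the best single predictor, and it is used unconditionally. A reader might infer that all covariate adjustment depends on baseline tests. The text does not support that, and the point is confined to the further covariables.
- **The trigger is not clearly a significance test, and an unseen analysis plan may set the threshold and the list.** The first half stands: only the order of the sentences implies that the t and chi-square tests decide. But the conditional rule itself is stated positively, so the point does not rest on missing detail. Any rule keyed to observed imbalance has the same weakness, whatever threshold is set.
- **The discretion is limited.** This stands. A reader might infer that adjustment could be chosen to suit the result. The stated trigger is a T0 comparison, not the outcome. A reader might also expect inflated type I error, and the simulation shows none. Nor are the covariables purely descriptive: they are the evident pool for the conditional adjustment.
- **The gain is assumed and may be small.** This stands in part. The R-squared must hold after T0 adjustment, and HADS overlaps with the psychological distress score at T0. The trial is sized for 0.5 SD, so the power figures at 0.28 SD illustrate the contrast between methods rather than this trial's power.

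A reader might also count the eight outcomes at T0 with the five covariables, giving 13 tests and 1 − 0.95^13 = 0.487, or about half of trials. That overstates the problem, because each outcome's T0 value is already in its own analysis and an imbalance there does not switch that model. The Measures section also ties participant characteristics to the covariables.

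**Conclusion.** The point holds in a limited form. For covariables other than the outcome's own T0 value, observed imbalance decides whether they are used, and after simple randomization that imbalance carries no information on prognosis. With 5 to 7 independent tests at an assumed 5% level, the model would switch by chance in about 23% to 30% of trials. In the remaining 70% to 77% the covariables are left out, including the three that the Background connects to service use.

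The consequence is a data-dependent model and lost precision. If the covariables explain an assumed 10% to 20% of the variance remaining after T0 adjustment, a fixed list would cut residual variance by about that much, and the stated rule would forgo nearly all of it. The validity of the test is not in question. This is a free improvement to the analysis wording, not a flaw that threatens the trial's conclusions.

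**What to change.** Before any outcome data are seen, name a short covariate list from the variables already collected at T0, for example DBMA, HADS and perceived economic situation. Include it, with the T0 value of the outcome, in every outcome model whatever the baseline comparison shows. In the six-month repeated measures analysis, let the covariate effects differ by time. With complete data, covariates entered only as main effects do not alter the group-by-time comparison.

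Describe baseline characteristics by group without using tests to choose covariates. Keep any adjustment prompted by an observed imbalance as a labelled sensitivity analysis.

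The cost is a change of analysis wording. No new data, visits or participants are needed. A few degrees of freedom are spent on the covariates, which is negligible with 400 participants.

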#### Sample size and statistical power

When analyzing quantitative data, we must take into account that part of the effect is potentially associated with each of the eight case management nurses. The intra-nurse or intracluster correlation (ρ) is unknown, however, and is specific to each variable. On the other hand, given that series of standardization measures will be implemented to minimize nurse-specific effects, we anticipate that the intracluster correlation will not be higher than 0.10. Sample size was therefore calculated using this maximal anticipated ρ-value. Results indicated that a standardized effect size (ES) of 0.5 (qualified as medium [73]) will be detectable with two groups of 200 participants (25 per nurse) for a two-tailed test with the α level set at 0.05 and a power of 80% [74]. An ES of at least this magnitude can be expected since it was observed in a previous study [75] and in unpublished data from the CSSS de Chicoutimi. An ES of at least 0.5 also represents the clinically significant effect needed to justify the pragmatic integration of the intervention into the services already provided. For example, in the case of patient empowerment, the ability to detect an ES of 0.5 translates into the capacity to detect any difference of at least half a point within different domains of the heiQ, since the overall standard deviation is about 1 point [76]. The detection of smaller differences is irrelevant since it is not clinically significant.

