### Strengths and limitations

The study design will not allow us to determine the individual effects of each component (case management and self-management group support) of the intervention. It was conceived in order to evaluate the addition of the self-management component for some patients who can benefit from it according to primary care practitioners’ perspective. Independent applications for funding are planned in order to evaluate the effects of each component in a near future. A contamination bias could occur between the case management nurses and the nurses involved with the patient control group. Several precautions will be taken to minimize this bias. First, no nurse will monitor both experimental group and control group. Discussions between nurses caring for the groups will be kept to a minimum with respect to the intervention and the new follow-up methods developed during the first six months of implementation. The implementation analysis will shed a qualitative light on this phenomenon. The presence of eight case management nurses raises the possibility of a “cluster” effect at the analysis level, which will be verified. However, this should be minimal since many precautions will be taken to reduce it: proper training of eight case management nurses to ensure standardization; the important role of the Clinical Project Coordinator in maintaining a comparable level of intervention among the eight nurses; regular discussions (every 1.5 months) among case management nurses. Repeat surveys induce a learning effect; however, the time-lapse between each survey questionnaire will be sufficient for the effect to be minimal. Regarding external validity, the pragmatic nature of the effects evaluation favours generalization. Analysis of the implementation process will identify the factors to be considered and the conditions to be put into place to support implementation of the intervention in other Quebec FMG.

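### The nurse term enters the analysis only if a nurse effect is found, by an unstated criterion; it should be fitted always

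*Protocol article*

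**What the plan says.** Under Sample size and statistical power, the protocol article states that part of the effect may belong to the eight case management nurses and has to be allowed for. It says that the ICC is unknown and differs by variable, that "we anticipate that the intracluster correlation will not be higher than 0.10", and that "Sample size was therefore calculated using this maximal anticipated ρ-value". It concludes that "a standardized effect size (ES) of 0.5 (qualified as medium [73]) will be detectable" "will be detectable with two groups of 200 participants (25 per nurse) for a two-tailed test", at a two-sided 5% level and 80% power.

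Under Data analysis plan, the three-month outcomes are compared by ANCOVA on the baseline score and the six-month outcomes by repeated-measures ANOVA. Neither has a nurse term. The nurse enters only by a conditional rule: "if a nurse effect is present (non-null intracluster correlation), despite efforts at standardization, multi-level analysis will be conducted".

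Under Strengths and limitations, the cluster effect is expected to be small because of training and coordination, and is to be checked. The same section says that "no nurse will monitor both experimental group and control group", and it also mentions nurses who look after the control group.

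**The concern.** The two sections treat the same feature differently. For the sample size, nurse clustering is taken as given at the largest ICC expected. For the inference, it counts only if the data show it. The words in brackets in the rule do not say whether a p-value, an estimate above zero or something else decides. Because the article says the ICC is specific to each variable, the check would naturally be made outcome by outcome, so different outcomes could be analysed by different models, each chosen from its own data.

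A check on eight nurses is weak when the ICC is small, and standardization is meant to make it small. A non-significant nurse test is then poor evidence that clustering can be ignored. When a real nurse effect is missed, the standard error of the group difference is too small and the nominal 5% test is not a 5% test.

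**Working it through.** **Inputs.** Two nurses in each of four practices gives 8 (Case management by FMG nurses). Fifty experimental patients per practice gives 200, so 25 per nurse (Study population). There are 200 controls on usual care for six months. ICC at most 0.10, effect size 0.5, two-sided 5%, power 80% (Sample size and statistical power). ICCs of 0.05 and 0.02 are our assumptions. Outcomes have unit variance, and the ICC is taken to apply to the outcome as analysed.

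**1. The stated power.** Design effect = 1 + (25 − 1) × 0.10 = 3.4.

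- Both arms clustered: SE = √(2 × 3.4/200) = 0.184; 0.5/0.184 = 2.71. Power is 77.4% by the normal approximation and 71.3% by t on 14 df. The detectable effect at 80% is 2.80 × 0.184 = 0.517.
- Experimental arm only: SE = √((3.4 + 1)/200) = 0.148; 0.5/0.148 = 3.37. Power is 92.1% (normal), 86.9% (Satterthwaite t, 11.7 df) or 82.3% (t, 7 df). The detectable effect is 0.416 (normal).

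None of these is exactly 80%. The nearest are 77.4% (both arms) and 82.3% (one arm), so the figure does not reveal which structure was used.

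**2. How often the nurse effect is found.** With 8 nurses × 25, the one-way F statistic on 7 and 192 df is distributed as F multiplied by 1 + 25ρ/(1 − ρ). The chance of detection is therefore P(F > c/[1 + 25ρ/(1 − ρ)]), where c is the 5% critical value for a significance test, or 1 if any estimate above zero counts.

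| True ICC | Found, p < 0.05 | Missed, p < 0.05 | Found, estimate > 0 |
|---|---|---|---|
| 0.10 | 80% | 20% | 97% |
| 0.05 | 52% | 48% | 88% |
| 0.02 | 22% | 78% | 70% |
| 0 | 5% | – | 43% |

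**3. Type I error if nurses are ignored.** With clustering in one arm, the true variance exceeds the assumed one by the factor (design effect + 1)/2. At ICC 0.10 this is (3.4 + 1)/2 = 2.2, so the error is 2 × [1 − Φ(1.96/√2.2)] = 18.6%. At 0.05 (design effect 2.2, factor 1.6) it is 12.1%. At 0.02 (design effect 1.48, factor 1.24) it is 7.8%. In simulation, restricted to trials where the 5% nurse test misses the effect, the rates are about 19%, 12% and 8%. A non-significant nurse test therefore gives no protection.

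**4. Type I error of the whole rule** (100,000 simulated trials per ICC; experimental arm clustered, controls independent; Satterthwaite test when the nurse term is used).

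| True ICC | Always model nurse | Two-stage, p < 0.05 | Two-stage, estimate > 0 |
|---|---|---|---|
| 0.10 | 5.2% | 6.5% | 5.2% |
| 0.05 | 5.2% | 7.0% | 5.0% |
| 0.02 | 5.1% | 6.3% | 4.5% |

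The overall inflation is small for a simple reason. At ICC 0.10 the missed trials contribute about 0.20 × 19% = 3.8 points. The other 80% contribute only about 6.5 − 3.8 = 2.7 points, because trials in which the nurse effect is found are those with a large estimated between-nurse variance.

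**The case against.** The strongest reply is that the 5% pre-test is ours: the article names no p-value. Read literally, a non-null ICC could mean any estimate above zero, and then the overall error stays near 5%. Even under the 5% test, the error of the planned procedure is 6 to 7%, and at the only ICC the article gives, the effect is found 80% of the time. The article also recognises clustering, takes steps to limit it and commits to a multi-level model if it appears, and a fuller plan may state the trigger. All of this stands, and it limits the size of the point. It does not remove it: the article itself lays down a data-dependent rule, and whether the rule is harmless depends on a criterion it does not give.

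A reader might go further and infer that the power calculation wrongly clustered the control arm, that this arm has no clustering at all, and that the trial is underpowered. The documents do not support this. The caseload of 25 follows the mention of two groups, but 8 × 25 = 200 fills only the experimental arm, so the bracket may simply describe that arm. Controls have no case management nurse during the comparison, but the article mentions other nurses caring for them, with no numbers or caseloads. If both arms were taken as clustered by 25, that is conservative relative to clustering in the experimental arm alone.

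**Conclusion.** The point holds as a should-fix. Nurse clustering is required for the sample size but conditional for the analysis, and the condition is undefined. Under an assumed 5% pre-test, a real nurse effect is missed in 20%, 48% and 78% of trials at ICC 0.10, 0.05 and 0.02, and the unclustered test in those trials runs at about 19%, 12% and 8%. Those are conditional rates. It would be wrong to quote them as the trial's type I error, which is about 6 to 7% under that rule and near 5% if any positive estimate triggers the multi-level model. The figures rest on equal caseloads of 25, independent controls and, for the two smaller ICCs, values we chose.

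The power statement needs a clarification only. Its 80% lies between 77% (both arms clustered, normal approximation) and 82 to 92% (experimental arm only), so the structure cannot be identified, and no shortfall is shown.

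**What to change.** Remove the condition. For every outcome, fit a nurse random effect in the experimental arm whatever the estimated ICC, with each control patient as a separate unit (a partially nested mixed model) and Satterthwaite or Kenward-Roger degrees of freedom. If control patients also turn out to be grouped by nurse, say how that is handled. In the sample-size section, add one sentence stating which arm or arms are clustered and the degrees of freedom used.

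The cost is wording, with no extra patients. Intervals are slightly wider when the true ICC is near zero: about 27 rather than 398 df at ICC 0, so a multiplier of 2.05 rather than 1.97, or about 4%. At ICC 0.10 and effect size 0.5, power with 200 per arm stays at 86.9% (Satterthwaite) or 82.3% (7 df), above the planned 80%.
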